**R**each	-LC- consultee-centered training focusing on recruitment at schools and clinics -Develop a packaged implementation blueprint- referral process	-LC training and consultation sessions -BHF recruitment training -Recruitment activities	-BHF recruitment training -Recruitment activities	-Number, proportion, & representativeness of eligible families screened	C_LC_-C_PO_/E_LC_-E_PO_	Cost of per additional person recruited
**E**ffectiveness	-BHF program training and delivery	-All LC activities -BHF program training and delivery	-BHF program training and delivery	-Reduction in BMI *z*-scores	C_LC_-C_PO_/E_LC_-E_PO_	Cost per additional BMI *z*-score reduced
**A**doption	-Fund and contract	-Response to RFA from potential community stakeholders and organizations	-Response to RFA from potential community stakeholders and organizations	-Objective count of communities responding to RFA and contracted to implement BHF	C_all_/E_all_	Cost per community adoption
	-LC- consultee-centered training with focus on BHF cohort adoption -Develop a packaged implementation blueprint- BHF online training resources & package	-LC training and consultation sessions -Online training and program packaging -BHF program training and delivery	-Online training and program packaging -BHF program training and delivery	-Objective count of # of BHF cohorts initiated	C_LC_-C_PO_/E_LC_-E_PO_	Cost per additional cohort initiated
**I**mplementation	-LC- consultee-centered training with focus on implementation fidelity	-LC training and consultation sessions	None	-Average fidelity scores from the direct observation	C_LC_/E_LC_-E_PO_	Cost per additional changes in fidelity scores
	-Develop a packaged implementation blueprint- BHF online training resources & package	-Online training and program packaging	-Online training and program packaging	-Average knowledge check scores from BHF online training resources -Summarized implementation fidelity assessed via direct observation.	C_all_/E_all_	Cost per knowledge score/unit of implementation fidelity
**M**aintenance- setting level	-LC- sustainability action planning	-LC training and consultation sessions	None	-Objective count of BHF cohort continued	C_LC_/E_LC_-E_PO_	Cost per additional 3rd cohort initiated

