### Eligibility, recruitment, and allocation

#### Community level

Applying the community engagement approach, the research team and the BHF-CAB disseminated the RFA within and outside their organizations and networks (i.e., applying network weaving strategy) and documented that communities across all 93 counties received the RFA. Eight communities with broad geographic distribution responded to the RFA of which seven rural communities in Nebraska completed a full proposal and were selected as the participating communities for the HEI trial. We then ranked the seven applications in a descending order and allocated the odd-numbered rankings to the (BHF-LC) and the even-numbered rankings to the package-only (BHF-PO) condition [23]. This exercise resulted in four communities in the BHF-LC condition and three communities in the BHF-PO condition. All communities that implement the PWMI will have access to the BHF Online Training Resources and Program Package that includes all of the materials necessary to implement and evaluate the BHF intervention.

Communities assigned to the BHF-PO condition are required to complete a memorandum of agreement (i.e., obtaining formal commitment strategy) to report on the implementation of the PWMI and to use pragmatic evaluation strategies for reach and effectiveness outcomes and to provide de-identified program data for baseline, 6, and 12 months. These communities will also have technical support as needed related to package function, but no other facilitation. Communities allocated to the BHF-LC condition will participate in LC training lessons with additional embedded implementation support activities with a goal to (1) develop local strategies to screen and engage families through the BMI Reporter in schools or clinical screening and referral, (2) increase implementation fidelity, and (3) plan for sustainability.

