#### Individual level

Recruitment will be completed by selected communities through school BMI report cards, physician referral, local advertisements, and through word-of-mouth based on locally available resources and guided by the BHF Online Training Resources and Program Package. All materials are designed for local adaptation based on location, time of the session, clinical and school partners, and form of recruitment used. For BHF participation, families will be eligible if they have a 6- to 12-year-old child with a BMI percentile ranking at or above the 95th percentile. Children with major cognitive or physical impairments, parents or children with a contraindication for physical activity and families participating in a concurrent PWMI will be excluded. According to our previous studies [20–22], 8–12 families per cohort would be ideal with a minimum of 5 families and a maximum of 12 families in each cohort. The study goal is to enroll 12 families (*n*=30–48 individuals) per cohort and 2 cohorts per community. With a total of 7 communities recruited, the total PWMI intervention participants are approximately 420–672 parent-child dyads.

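### Table 1 subtracts raw counts between arms of four and three communities, so the Reach, cohort-Adoption and Maintenance ratios show an LC effect that comes from the unequal allocation

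*Protocol article*

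**What the plan says.** **Allocation.** Seven ranked applications were split by a rule that "allocated the odd-numbered rankings to the (BHF-LC) and the even-numbered rankings to the package-only (BHF-PO) condition" (Community level). The result is stated there: "This exercise resulted in four communities in the BHF-LC condition and three communities in the BHF-PO condition".

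**Goal per community.** It is the same in both arms: "The study goal is to enroll 12 families (*n*=30–48 individuals) per cohort and 2 cohorts per community" (Individual level).

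**Effects (Table 1, Study design).**
- Cohort adoption is "Objective count of # of BHF cohorts initiated", and its ratio is read as "Cost per additional cohort initiated".
- Maintenance is "Objective count of BHF cohort continued", read per additional third cohort.
- Reach lists a number, a proportion and representativeness, but its ratio is read per additional person, which is a count scale.
- LC Implementation uses "Average fidelity scores from the direct observation". Package Implementation uses average knowledge scores and summarised fidelity.

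The section Effect measurement repeats the count definitions.

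**Ratios (Table 1).** Reach and cohort adoption use (C_LC − C_PO)/(E_LC − E_PO). LC Implementation and Maintenance use C_LC/(E_LC − E_PO), with the PO cost entered as none. Package Implementation uses C_all/E_all.

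**Costs.** The section on labor costs adds up time multiplied by wage over people and activities to a total per strategy. It gives no per-community figure.

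**Unit.** Overview of economic evaluation names the seven communities as the unit of analysis. No formula, outcome or interpretation in Table 1 applies this to C or E.

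**The concern.** A raw count grows with the number of communities that can contribute to it. Subtracting a three-community count from a four-community count therefore mixes any LC effect with one additional community's output. The same holds for a difference in summed costs wherever a PO cost is subtracted.

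Reach, adoption and sustainability belong to the trial's primary aim, and these rows are their economic comparison. Followed as written, the formulas can report a cost per additional cohort when LC added none, or when LC communities did worse than PO communities. Collecting more data in the same 4:3 split would not remove the shift.

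**Working it through.** **1. The plan's own figures.** Ranks 1, 3, 5, 7 go to LC (4) and ranks 2, 4, 6 to PO (3), as stated. Cohorts: 7 × 2 = 14. Individuals: 14 × 30 = 420 and 14 × 48 = 672, which reproduces the stated range. (The plan writes "With a total of 7 communities recruited, the total PWMI intervention participants are approximately 420–672 parent-child dyads", but the range matches individuals; 14 × 12 = 168 families. This does not affect the point.)

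**2. Effects when all communities perform equally.**

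| Outcome | LC total | PO total | Difference of totals | Difference per community |
|---|---|---|---|---|
| Cohorts (2 each) | 4 × 2 = 8 | 3 × 2 = 6 | +2 | 0 |
| Families (24 each, standing in for the Reach count) | 4 × 24 = 96 | 3 × 24 = 72 | +24 | 0 |
| Third cohorts (1 each) | 4 | 3 | +1 | 0 |

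The totals tie when 4·e_LC = 3·e_PO, that is e_LC = 0.75·e_PO (1.5 vs 2 cohorts). At 1.75 vs 2, LC is 12.5% worse per community, yet the totals show 7 − 6 = +1.

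**3. Cost difference in Reach and Adoption.** Let c be the non-LC cost per community and L the LC cost per LC community. Neither is in the document, so a range is shown.

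C_LC − C_PO = 4(c + L) − 3c = c + 4L. The LC cost actually incurred is 4L.

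| L/c | c + 4L | 4L | Overstatement |
|---|---|---|---|
| 0.25 | 2c | 1c | 2× |
| 0.5 | 3c | 2c | 1.5× |
| 1 | 5c | 4c | 1.25× |

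**4. Net effect on the Adoption ratio.** Totals give (c + 4L)/(4·e_LC − 3·e_PO); per community it is L/(e_LC − e_PO). With L = 0.5c and e_PO = 2:

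| e_LC | Totals | Per community | Totals compared with per community |
|---|---|---|---|
| 2 | 3c/2 = 1.5c | undefined | a ratio where there is no effect |
| 2.5 | 3c/4 = 0.75c | 0.5c/0.5 = 1.0c | favours LC |
| 3 | 3c/6 = 0.5c | 0.5c/1 = 0.5c | equal |
| 4 | 3c/10 = 0.30c | 0.5c/2 = 0.25c | against LC |

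**5. Maintenance.** Let m be continued cohorts per community. Totals give 4L/(4·m_LC − 3·m_PO). Per community, L/(m_LC − m_PO) = 4L/(4·m_LC − 4·m_PO). The first denominator is larger by m_PO, so for any real LC gain the ratio looks better for LC whenever m_PO > 0.

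**6. Implementation.** A difference in mean scores is not shifted by the extra community. The cost is a sum, however. If LC cost were 1 unit per community and the mean difference 10 points, the ratio would be 0.1, 0.2, 0.3 or 0.4 for 1, 2, 3 or 4 LC communities. Likewise C_all/E_all, with 1 cost unit per community and a mean score of 80, is 7/80 = 0.0875 for 7 communities and 14/80 = 0.175 for 14. Performance is unchanged in both cases.

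**The case against.** **The community is named as the unit of analysis, and a journal article condenses.** Table 1 never says that its entries are arm totals, and a per-community reading would fit the unit-of-analysis sentence. This stands in part: the totals reading is inferred from the count definitions, the per-additional-unit readings and the summed costs. But the article does print the formulas, the outcome scale and the interpretation, and none of them uses the unit. An analyst who follows Table 1 gets the shifted result.

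**A reader might infer that the ratios are biased toward LC throughout.** Step 4 shows otherwise. In Adoption and number-based Reach the inflated effect and the inflated cost pull in opposite directions, and the net sign depends on c, L and the true effect. Only Maintenance has a fixed direction.

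**A reader might infer that the cost is overstated 8, 6 or 5 times** by comparing c + 4L with L. That sets an arm total against a per-community cost. Like for like, against 4L, the factors are 2, 1.5 and 1.25, and they concern the numerator only, not the ratio.

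**A reader might infer that the fidelity ratio is four times too large.** That needs LC cost to rise in proportion to communities. Table 2 lists much shared research-team work, such as preparing and delivering learning sessions, so the dependence holds only as far as costs scale. A programme-level cost per point is also a possible reading of that row.

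**A reader might extend the point to every row.** The proportion in Reach is free of it. The fund-and-contract row divides one overall total by another, with no arm subtraction. The BMI z-score effect is not a count, and Sensitivity analysis resamples cost-effect pairs from the trial data, which suggests unit-level values.

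**It is a pilot.** Challenges and limitations concedes low power and does not address use of the results by decision makers. That limits the consequences, but imprecision is a separate matter from a fixed shift, which that section does not mention.

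**Conclusion.** The point holds for the count rows as written. Under equal performance at the planned goal, the 4:3 split alone yields +2 cohorts and +24 families, and +1 third cohort if every community runs one. LC can be up to 25% worse per community before the count advantage disappears. In Reach and Adoption one community's non-LC cost is added to the incremental cost, so the ratio is wrong in a direction that cannot be stated in advance. In Maintenance the distortion favours LC whenever PO continues any cohort. The Implementation rows have a mismatch of units, not a spurious effect.

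This rests on reading C and E as arm totals, on the planned 2 cohorts of 12 families per community as the equal-performance case, and on assumed values of c and L for every cost figure.

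**What to change.** In Table 1:
- For Reach, cohort adoption and Maintenance, define C and E as means per community in each arm before subtracting: (mean cost per LC community − mean cost per PO community)/(mean outcome per LC community − mean outcome per PO community). Where PO has no cost, its mean is zero. The per-additional-unit readings can stay, because the per-community units cancel.
- For both Implementation rows, put the cost on the same per-community unit as the score.
- State that when the effect difference is zero or negative, costs and effects are reported side by side without a ratio.

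The cost is a change of wording in Table 1 and a division by 4, 3 or 7 in the spreadsheet. No new data are needed and the allocation is untouched.

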	**Implementation** -Observed adherence to protocol and family engagement at each BHF session -Instructor self-reported fidelity at each BHF session	-Create learning session materials -Delivery learning sessions -Provide individual/group consultation -Conduct knowledge/fidelity checklist -Provide feedback at each learning session -Complete pragmatic evaluations	-Research team -Research team -Research team -Research team -Research team -Research team	BHF-LC	Mid-late	Frequency of the training sessions focusing on implementation	Duration of the sessions
	**Maintenance** -Survey/checklist at 12 months -Objective count of sustained implementation of cohorts in the year following completion of the LC intervention	-Develop sustainability needs assessment checklists -Develop funding matrix development tools -Develop key partner identification and engagement -Develop an ongoing assessment & feedback -Conduct sustainability needs assessment -Examine current and future resources, payer and payment models -Integrate into regular learning meetings & action periods	-Research team & CAB -Research team -Research team -Research team & CAB -Research team -Research team & CAB -Research team	BHF-LC	Late	Frequency of activities/events focusing on maintenance	Duration of the activities

*BHF* Building Healthy Families, *LC* learning collaborative, *PO* Package only, *CAB* community advisory board, *LOI* Letter of intent

^a^Costs are divided among RE-AIM (reach, effectiveness, adoption, implementation, and maintenance) outcomes and are estimated with actions/activities specified for that specific outcome

^b^Costs are divided among implementation outcomes associated with the strategy, based on the activities specified in the action column

^c^Preparation time and travel time (if any) and post-session follow-up (e.g., summary note) are also included

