##### Data analysis

Table 1 summarizes the proposed within-trial economic evaluation and associated costs and outcomes by the RE-AIM indicators. The cost-effectiveness of D&I strategies is assessed by combing their associated costs and outcomes using an incremental implementation cost-effectiveness ratio [33] (ICER) if a strategy is simply applied to the BHF-LC with the BHF-PO as the comparison group or average implementation cost-effectiveness ratio [34] (ACER) if a D&I strategy is applied in both the BHF-LC and BHF-PO conditions (and thus no comparison group). The interpretation is similar to the interpretation for a trationdtional ICER. An ICER is interpreted as the extra cost incurred for the intervention to achieve an extra 1 unit of increase in outcomes (reach, adoption, implementation, and maintenance) measured, whereas ACER represents the cost associated with a one-unit change on given measures for the outcome of interest. For example, the ACER for the fund and contract dissemination strategy to increase the adoption of the BHF program, at the micropolitan and surrounding rural areas is described as the costs associated with one community responding to RFA and contracted to implement BHF.

Similarly, the cost-effectiveness of the BHF program is determined by the total LC costs (BHF-LC group only) and the BHF program costs consisting of training, recruitment, program delivery, and post-follow-up, and the effect of BMI *z*-score reduction at 6 and 12 months. The ICER result is interpreted as the cost for an additional unit decrease in BMI *z*-scores between the BHF-LC and BHF-PO conditions.

To ascertain whether a given ICER/ACER is cost-effective, we will compare them to thresholds that are based on findings from previous economic research [13].

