These stem from a fundamental difference between implementation economic evaluation and traditional economic evaluation. The former addresses the resources (e.g., implementation activities) needed to encourage adoption, implementation, and sustainability of the EBI, whereas the latter focuses primarily on the start-up and ongoing costs of the EBI itself [43]. D&I strategies can vary in their intensity and resource use as well as their effectiveness in aiding the implementation of EBIs [6]. In this economic evaluation protocol targeting D&I strategies, we attempt to identify and present the strategy costs across RE-AIM dimensions to clarify sometimes fuzzy boundaries between these strategies. Moreover, to conduct cost assessment across RE-AIM dimensions, it may be implicitly assumed that one implementation strategy has an impact on only one implementation outcome, which is likely not the case in the present study. For example, the strategy of “developing packaged implementation blueprint” has impacts on three implementation outcomes (reach, adoption, and implementation). Even a fund and contract dissemination strategy with a primary goal to increase adoption embedded the need for network weaving to improve implementation and likely sustainability over the life course of the program. To not overestimate the cost-effectiveness (i.e., double-counting) of a D&I strategy, we deliberately attributed the activities within the strategy to an associated primary implementation outcome target for the given strategy.

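### The package's fidelity ACER credits learning-collaborative gains to the package at no collaborative cost, and the LC ICERs set a share of LC cost against the effect of the whole LC

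*Protocol article*

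**What the plan says.** **Package ratio.** In Table 1 (Study design), the second Implementation row gives the package the ratio C_all/E_all. The cost in both condition columns is "Online training and program packaging". The effect is the knowledge-check score and "Summarized implementation fidelity assessed via direct observation", and the result is to be read as "Cost per knowledge score/unit of implementation fidelity". The Data analysis section uses an ACER "if a D&I strategy is applied in both the BHF-LC and BHF-PO conditions (and thus no comparison group", so E_all pools the conditions.

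**LC fidelity ratio.** The row above it covers "LC- consultee-centered training with focus on implementation fidelity". Its ratio is C_LC/(E_LC − E_PO), on "Average fidelity scores from the direct observation".

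**Cost split.** Footnote b to Table 2, marked on both the package and the LC, says: "Costs are divided among implementation outcomes associated with the strategy, based on the activities specified in the action column". Footnote a says the same for RE-AIM outcomes in general. The Discussion offers this as protection against double-counting and against overstating cost-effectiveness: "we deliberately attributed the activities within the strategy to an associated primary implementation outcome target for the given strategy". The same paragraph accepts that a strategy acting on a single outcome is probably not what happens in this study.

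**The concern.** A cost-effectiveness ratio is interpretable only if its numerator holds the cost of whatever produced its denominator. Two groups of ratios in Table 1 depart from this.

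First, LC communities receive the package plus the LC. Any fidelity the LC produces enters the package's denominator, while no LC cost enters its numerator.

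Second, the trial compares the whole LC with no LC, so E_LC − E_PO is the effect of the whole LC. The LC cost placed over it is only the part assigned to that outcome. Dividing the cost while leaving the effect undivided pushes the ratio in the favourable direction, which is the opposite of the purpose stated in the Discussion.

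The consequence is practical. The Data analysis section will compare ICERs and ACERs with thresholds from earlier research. The Background and Conclusion also say the results should help communities and payers choose strategies for particular outcomes.

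**Working it through.** The article gives no cost or effect figure for these ratios, so there is nothing to reproduce. The algebra below gives the direction, and assumed values illustrate the size.

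**Package ACER for observed fidelity**

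Inputs from the documents:
- 4 LC and 3 package-only (PO) communities (Eligibility, recruitment, and allocation; ranks 1, 3, 5 and 7 against 2, 4 and 6).
- Package cost in the numerator for both conditions (Table 1).

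Assumptions:
- Each community counts equally in the pooled score.
- Package cost per community is the same in both conditions.
- PO fidelity is f on a 0–100 scale, and the LC adds d points.

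Formulas:
- E_all = [4(f + d) + 3f]/7 = f + 4d/7.
- Pooled ACER ÷ PO-only ACER = f/(f + 4d/7).

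With f = 70:

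| d | E_all | Ratio | Pooled ACER is |
|---|---|---|---|
| −5 | 67.14 | 1.043 | 4% too high |
| 0 | 70.00 | 1.000 | unbiased |
| 5 | 72.86 | 0.961 | 4% too low |
| 10 | 75.71 | 0.925 | 8% too low |
| 20 | 81.43 | 0.860 | 14% too low |

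Over f = 60 to 80 and d = 5 to 20 the ratio runs from 0.84 to 0.97. Table 1 and Table 2 do not list the same package activities under Implementation. That leaves the size of the numerator unclear, but it does not alter this factor, because the per-community cost cancels.

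**LC ICERs**

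Let C be total LC cost, s the share assigned to one outcome, ΔE = E_LC − E_PO, and p the fraction of ΔE produced by LC activities costed to other outcomes.

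- Fidelity and Maintenance rows (LC cost only): the planned ICER is sC/ΔE. The ratio of those activities' cost to their own effect is sC/[(1 − p)ΔE]. Planned ÷ own-activity = 1 − p, which is 1.00, 0.75 and 0.50 for assumed p of 0, 0.25 and 0.50.
- The same rows on full LC cost give C/ΔE, so planned ÷ full = s. An equal four-way split (s = 0.25) would put the planned ratio at a quarter of the full-cost ratio. That is the distance to an upper bound, not a bias.
- Reach and cohort-adoption rows: the numerator is C_LC − C_PO and also carries recruitment, or package and delivery, cost. Call that non-LC cost difference K. Planned ÷ full = (sC + K)/(C + K), which is nearer to 1 than s whenever K > 0.

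**Is p above zero?** The text suggests so:
- Table 2 lists the same six LC activities, with the same mid-to-late timing, under Adoption and under Implementation. The action column on which footnote b relies therefore cannot separate these two outcomes.
- The BHF-LC section describes training embedded in the learning sessions as serving reach, fidelity and sustainability together.
- The Maintenance row of Table 2 folds its work into the regular learning meetings.

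**The case against.** The strongest reply is that the split is deliberate and disclosed. Challenges and limitations gives the pilot's goal as separating costs by strategy and by outcome. The BHF-LC section sequences the learning sessions by topic (reach, then implementation quality, then maintenance), and Table 2 counts sessions by focus. If the activities were fully separable, p would be zero and the LC ratios unbiased. Charging the whole LC to each of four outcomes would count its cost four times. This stands as a reason to keep the split ratios and to treat the full-cost ratio only as an upper bound.

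A reader might infer that every ratio in Table 1 is affected, that the LC ratios are several-fold too low, or that all errors favour the strategies. The documents do not support this:
- The Effectiveness row already carries all LC activities, and the fund-and-contract ratio concerns responses obtained before communities were allocated.
- The several-fold figure is 1/s against an upper bound, and the Reach and cohort-adoption numerators are not LC cost alone.
- The direction depends on the LC raising fidelity and on spillover between outcomes.

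Nor do the documents call for moving the knowledge-check ACER to package-only communities. Those scores come from online modules that both conditions use, and no LC effect on them is shown. The fidelity gain does appear in both the package and the LC ratios, but the two are not summed. What matters is the mismatch inside the package ratio.

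The rule that a strategy used in both conditions has no comparator does not rescue that ratio. The package-only communities provide a fidelity score without the LC.

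**Conclusion.** The concern holds in two parts.

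The package's observed-fidelity ACER is misspecified. It is too low by the factor f/(f + 4d/7) whenever d > 0, or about 4% to 14% for f = 70 and d = 5 to 20. Those scores are assumed, as are equal community weights and equal package cost per community. The bias is modest, but it follows from the formula in Table 1 and is cheap to remove.

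The LC ICERs for Reach, cohort adoption, Implementation and Maintenance are too favourable to the extent that LC activities affect outcomes to which they are not costed. The Discussion concedes such spillover and Table 2 suggests it. Its size cannot be determined from the document. The Discussion's claim that attributing activities to one outcome prevents overestimation is wrong as it stands, because only the costs are divided.

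**What to change.** 1. **Table 1, package Implementation row.** Compute the observed-fidelity ACER from the package-only communities (C_PO/E_PO, per community) and show the LC communities' value separately. Allocate shared development cost over all seven communities. Loading it on three would raise that part of the per-community cost by 7/3. The knowledge-check ACER may stay pooled.
2. **Table 1, LC rows for Reach, cohort adoption, Implementation and Maintenance.** Keep the split ICERs, state that their LC component is an activity-based share, and report beside each one the ratio on full LC cost, labelled as an upper bound.
3. **Discussion.** Reword the double-counting sentence to say that the split avoids charging the same LC cost to several outcomes, and that it understates cost per unit of effect where activities spill over.

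No new data are needed. The cost is precision in item 1, where the ratio rests on three communities, and a less favourable second figure beside each LC ratio in item 2.
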